9.2.1. Haematuria positive/symptoms positive

9.2.2. Haematuria negative/symptoms positive

9.2.3. Haematuria positive/symptoms negative

9.2.4. Haematuria negative/symptoms negative

10. Recruitment rates will be measured via the number of invitations sent out versus uptake.

### Secondary and exploratory outcomes

Secondary outcomes include (1) self-test reporting via the mobile app or freephone, and this impact on sensitivity/specificity to detection of cancer, and (2) the acceptability of the reciprocal design (measured by the proportions of compliance/attendance/surveys at the end of the trial).

Exploratory outcomes include (1) Comparison of populations, demographics and cancer incidence in those who do/do not complete self-testing (comparing the characteristics where available including sex, age group, quintile of deprivation, smoking history). All participants who self-test will be flagged in National Cancer Registration and Analysis Service (NCRAS) for cancer diagnoses at 1, 2 and 3 years following the end of the trial. (2) The development of an artificial intelligence (AI) platform for the assessment of urine samples for cytology analysis for the future study will be measured by the accuracy of the AI read versus the manual read at the end of the trial. (3) The potential harm of cystoscopy adverse effects, specifically urinary tract infections requiring medical treatment, will be measured by the proportions of participants who have a Urinary Tract Infection (UTI) requiring medical treatment following cystoscopy at the end of the trial. (4) Development of a health economics model^23^ using the information from this feasibility study that could be used to develop a future community-based screening programme for BCa will be measured at the end of the study by: (4.1) Resource usage in each arm (number of clinics used, blood tests, ultrasound tests, extra NHS tests); (4.2) Rate of cancers and other illnesses per arm. (5) The addition of other urinary contents (leucocytes, nitrate, protein) in relation to the risk prediction of BCa will be measured by other positive test strip panels in addition to haematuria at the end of the trial.

### Data collection

Self-test results and questionnaire data will be captured in the bespoke mobile app and freephone system. The questionnaire will collect information on diabetes (diagnosis and management), smoking status, ethnic group, lesbian, gay, bisexual, and transgender (LGBT) identification, highest level of education, history of factory work as well as bladder symptoms (via a modified and unvalidated version of the UTISA Questionnaire^25^). Cohort 1 and 2 data collected at Early Detection Clinics will be entered into a REDCap^26^ database and will include height and weight, current occupation, previous longest occupation, concomitant medication, ultrasound results, urine cytology results and HbA1c results. Data for Cohort 1 and 2 participants who are subsequently referred for a 2ww, and consenting Cohort 3 participants, will be obtained via medical records to include results of cystoscopy, ultrasound/CT, cytology and cancer staging where applicable. At 14–30 days post cystoscopy, these participants will be contacted to collect information of any treated incidences of UTI following cystoscopy. Passive follow-up data (identification of cancer diagnosis and stage) will be collected through the NCRAS at 1, 2 and 3 years after the end of the trial for all participants who have self-tested (excluding withdrawals). Summary data will also be collected through NCRAS, requested by geographic area, for a population comparable to Cohort 2.

### Statistical analysis

We will present estimates of percentages, with 95% Wilson CIs, on a per cohort basis for the three trial endpoints that will allow assessment of feasibility and inform the subsequent more definitive trial. We will estimate acceptability (proportion of invitees consenting and returning a test strip), compliance (proportion of participants returning at least three or all six test strips), haematuria and glucosuria, proportion of positive outcomes for those referred to the Early Detection Clinic (positive cytology and/or USS for haematuria and HbA1c for glycosuria). We will assess the levels of BCa in the cohort identified by Early Detection clinic and at 3 years using National Disease Registration Service (NDRS, formerly NCRAS) and the accuracy of the haematuria test results including PPVs and NPVs for Cohorts 1 and 2 only. The urinary symptoms questionnaires will be summarised by cohort, by the proportions with each urinary symptom, and by overall urinary symptoms using mean, SD, median, minimum, maximum and quartiles. Missing values will be imputed as no symptom.

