#### Study aims and objectives

Three cohorts will be studied in this feasibility study. Each will address a separate aim, all of which are needed to develop a phase III prospective trial:

Aim 1: Cohort 1 will test compliance, prevalence of haematuria and BCa and the economics of the trial within a screening-engaged population. It might suggest that BCa screening works best when embedded within lung screening services. It will also test women and populations younger than typical for the highest risk BCa age group.Aim 2: Cohort 2 will test compliance, prevalence of haematuria and BCa, prevalence of glycosuria and undiagnosed diabetes within a high-risk community-based population.Aim 3: Cohort 3 will provide a positive predictive value (PPV) of the study tests (urine self-testing, urine cytology and ultrasound) as assessed in a population already referred in the NHS 2ww haematuria pathway.

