### Investigation of haematuria

Participants in Cohort 1 and those randomised to the haematuria arm of Cohort 2 will be investigated for the presence of haematuria (figures 1 and 2). If a single positive result is identified on research nurse review of the erythrocyte test parameter, then the participant will be invited to attend an Early Detection Clinic (run in a nearby GP surgery and staffed by study-employed or NIHR Clinical Research Network (CRN)-employed nursing staff) within 4–6 weeks of assessment of their results. At this clinic, participants will undergo a urinary tract ultrasound scan (USS) and provide a urine sample for cytology. Those with an abnormal USS (bladder or renal mass suggestive of cancer detected) or abnormal cytology will be referred by their GP or the research nurse team (following standard NHS 2ww criteria) to their local urology haematuria service for evaluation (flexible cystoscopy and additional assessments). We expect that around 20% of participants with self-testing haematuria will require referral. The test results for these participants will be obtained directly through the relevant urology departments and categorised into: BCa diagnosis, kidney cancer diagnosis, upper tract urothelial cancer diagnosis, urinary stones, infection or inflammation, stricture, clinically benign prostatic enlargement, post-TURP (transurethral resection of the prostate), diagnosis unclear/further tests planned, likely prostate cancer, no abnormal finding or other finding. Participants with normal USS and normal cytology, from the early detection clinic, will receive a letter explaining this and discharging them from the study. They will receive advice about the need to see their GP if they have urinary symptoms or VH. Their GP will receive a letter with advice about management of NVH. Participants without haematuria will receive a letter confirming their result and informed that their GP will also be notified of their results. They will be asked to seek a GP appointment if they develop urinary symptoms in the future. Participants in cohort 3 will undergo standard NHS assessment of haematuria as part of their referral process (regardless of their test strip results). This includes cystoscopy and upper tract imaging (typically CT urogram and USS).

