### Consent

On receipt of the postal urine self-testing kit, participants will be able to choose an action to take:

Consent to enter trial: those wishing to take part in the trial will be asked to consent to participate by agreeing to consent statements in the mobile App or freephone system, before proceeding to complete the study questionnaire, and then self-testing with the test strips. Invitees will be prompted prior to providing results to have read the Participant Information Sheet.Non-response: non-responders (ie, do not consent or provide test results via the mobile App or freephone)

Following a positive urine self-test result for haematuria (Cohort 1) and haematuria/glucosuria (Cohort 2) participants will receive a telephone call from a study research nurse to explain their results and schedule an Early Detection Clinic appointment.

This will be followed by the mailout of a second Patient information sheet (PIS) detailing what will happen at the Early Detection Clinic appointment. At the clinic, written informed consent will be obtained prior to any trial-specific procedures (online supplemental material). The chief investigator (CI) will ensure that those with delegated responsibility to obtain informed consent are duly authorised, trained and competent according to the ethically approved protocol, principles of Good Clinical Practice (GCP) and Declaration of Helsinki. The right of a participant to refuse participation without giving reasons will be respected.

10.1136/bmjopen-2023-076612.supp1Supplementary data

Cohort 3 participants will receive a self-testing kit including a study invitation letter and PIS detailing what will happen at the 2ww appointment (figure 3). The invitation letter will be from the routine care team at the participating urology department. On presentation to the 2ww appointment, written informed consent will be obtained prior to any trial-specific procedures. Translation via hospital interpreters is acceptable if required. The principal investigator will ensure that those with delegated responsibility to obtain informed consent are duly authorised, trained and competent according to the ethically approved protocol, principles of GCP and Declaration of Helsinki. The right of a participant to refuse participation without giving reasons will be respected. For Cohort 3, participation is mostly altruistic as the participants will already be in the NHS pathway and will have the gold-standard tests for detection of BCa.

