### Primary outcomes

This is a feasibility study and so there are multiple primary outcomes reflecting each stage of the study and what we need to understand for a larger phase III randomised controlled trial:

1. Acceptability of urine self-testing and the Early Detection Clinics will be measured by:

1.1. Proportion of invitees who report results for at least one test strip.

1.2. Proportion of participants who attend and consent for cytology and urinary tract ultrasound following detection of haematuria on self-testing.

1.3. Proportion of participants who attend and consent for HbA1c blood testing following the detection of glycosuria on self-testing.

2. Compliance with urine self-testing will be measured by;

2.1. The proportion of participants who report results for (i) all six test strips and (ii) three or more test strips.

2.2. The number of test strips returned on average in those who return at least one test strip.

3. Prevalence of haematuria will be measured from the proportions of participants with ≥1 test strip positive for haematuria.

4. Prevalence of glycosuria will be measured from the proportions of participants with ≥1 test strip positive for glycosuria.

5. Haematuria clinic outcomes will be measured via:

5.1. The proportion of participants with a positive or abnormal cytology in those where a urine sample is collected.

5.2. The proportion of participants who have an abnormal USS, who underwent scanning.

6. Glycosuria clinic outcomes will be measured via the proportions of those with an elevated HbA1c following collection of a blood sample.

7. Urinary symptoms will be measured via symptom scores from the urine symptoms questionnaire (as completed prior to self-testing).

8. BCa in the tested population will be measured via the proportions of BCa cases and corresponding stage in identified participants (excluding non-responders and withdrawals).

9. The accuracy of self-testing, cytology and USS will be measured via:

9.1. The sensitivity, specificity, PPV and negative predictive value (NPV) of the following in men and women with cancer as identified by cystoscopy results at the 2ww appointment

9.1.1. Self-testing (App vs freephone).

9.1.2. Cytology and ultrasound (separately and in combination) as a triage test in those with positive haematuria

9.2. The predictive value of symptoms in combination with self-testing:

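### The analysis section confines haematuria-test accuracy to Cohorts 1 and 2, contradicting Aim 3 and leaving out the one cohort that has cystoscopy whatever the strip shows

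*Protocol article*

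**What the plan says.** Statistical analysis, in a sentence that also covers bladder cancer found through the Early Detection Clinic and at 3 years in the registry, plans to assess "the accuracy of the haematuria test results including PPVs and NPVs for Cohorts 1 and 2 only". The section describes no accuracy analysis for Cohort 3.

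Other sections point the other way:

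- Study aims and objectives, Aim 3: "Cohort 3 will provide a positive predictive value (PPV) of the study tests", namely self-testing, cytology and ultrasound.
- Primary outcomes, 9.1: sensitivity, specificity, PPV and NPV of self-testing, and of cytology and ultrasound as triage, "in men and women with cancer as identified by cystoscopy results at the 2ww appointment".
- Investigation of haematuria: "Participants in cohort 3 will undergo standard NHS assessment of haematuria as part of their referral process (regardless of their test strip results"). That assessment includes cystoscopy and upper tract imaging. The Consent section says of the same patients that they "will have the gold-standard tests for detection of BCa".

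For Cohort 1 and the Cohort 2 haematuria arm, Investigation of haematuria says: "Participants without haematuria will receive a letter confirming their result". Strip-positives go to ultrasound and cytology. If both are normal they are discharged, and only those with an abnormal finding are referred on to cystoscopy. Data collection adds registry follow-up at 1, 2 and 3 years after trial end for everyone who self-tested, apart from withdrawals.

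**The concern.** The word 'only' is a stated rule. It excludes from the accuracy analysis the cohort that Aim 3 names for it, and an analysis plan cannot follow both passages.

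The cohorts that remain are poorly suited to outcome 9.1. Whether someone has cystoscopy there depends on the strip result and then on ultrasound and cytology, which are the tests being evaluated. Outcome 9.1.2 (cytology and ultrasound as triage in strip-positives) needs cystoscopy after normal triage, and Cohorts 1 and 2 do not supply it. The article lists the unknown sensitivity of a pathway without initial flexible cystoscopy among its own limitations. Within the trial, Cohort 3 is the only source of cystoscopy data that bears on this.

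At stake is a primary outcome with no coherent analysis population, in a study meant to inform the design of a larger trial.

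**Working it through.** The plan gives no accuracy figure or power calculation, so there is nothing to reproduce. The check compares verification by cohort, then adds arithmetic.

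**Who has cystoscopy within the trial pathway**

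| Group | Cystoscopy |
|---|---|
| Cohort 1 and Cohort 2 haematuria arm, strip-negative | No |
| Same, strip-positive, normal ultrasound and cytology | No |
| Same, strip-positive, abnormal ultrasound or cytology | Yes, by referral |
| Cohort 2 glycosuria arm, concealed haematuria | No haematuria work-up |
| Cohort 3, any strip result | Yes |

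**Inputs from the plan.** Expected enrolment is 800 (Cohort 1), 1200 (Cohort 2, about 600 per arm) and 500 (Cohort 3), from Sample size(s). Around 20% of strip-positives are expected to be referred, from Investigation of haematuria.

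**Assumed input.** The plan gives no expected strip positivity; I take 5–30%.

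**Share verified by cystoscopy**

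- Denominator: 800 + 600 = 1400.
- Strip-positive: 1400 × 0.05 = 70 to 1400 × 0.30 = 420.
- Referred: 0.20 × 70 = 14 to 0.20 × 420 = 84, which is 1% to 6% of 1400.
- Strip-positive, not referred: 70 − 14 = 56 to 420 − 84 = 336.
- Strip-negative: 1400 − 420 = 980 to 1400 − 70 = 1330.
- Concealed positives in the glycosuria arm: 600 × 0.05 = 30 to 600 × 0.30 = 180.

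The 80% of positives without referral does not depend on the assumed positivity. PPV is therefore affected as well as NPV.

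**What registry data can and cannot supply** (illustrations)

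- The screening yield cited in the Introduction is 17/2356 = 0.72%. Used as a prevalence, it gives 1400 × 0.0072 ≈ 10 cancers, and an uninformative test would have an NPV of 1 − 0.0072 = 99.3%. A high NPV says little here.
- Assume prevalence 1%, true sensitivity 50% and 20% strip-positive: 14 cancers, 7 of them missed, among 1120 strip-negatives. If half of the missed cancers surface in the registry, apparent NPV is 1 − 3.5/1120 = 99.7% and apparent sensitivity 7/(7 + 3.5) = 67%. If all surface, the figures are 1 − 7/1120 = 99.4% and 7/14 = 50%. This takes all strip-positive cancers as found.
- New cancers at an assumed 0.10–0.25% per year: recruitment from October 2022 to June 2023 puts the 3-year extract 3.0–3.7 years after testing, so 1400 × 0.0010 × 3.0 = 4.2 to 1400 × 0.0025 × 3.7 = 13.0. At the 1-year extract (1.0–1.7 years) they are 1400 × 0.0010 × 1.0 = 1.4 to 1400 × 0.0025 × 1.7 = 6.0. The time window changes the answer materially.

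**What Cohort 3 can supply** (500 enrolled; prevalence assumed)

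- Prevalence 5–15% gives 25–75 cancers assessed by cystoscopy. An observed sensitivity of 80% has a 95% Wilson interval of 61–91% with 25 cancers and 70–87% with 75.
- At prevalence 10%, sensitivity 70% and specificity 50%, there are 35 true positives, 225 false positives, 15 false negatives and 225 true negatives. Sensitivity is 35/50 = 70% (56–81%), PPV 35/260 = 13.5% (9.8–18.2%) and NPV 225/240 = 93.8% (90.0–96.2%).

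**The case against.** The best defence is that the sentence concerns cancers identified through the Early Detection Clinic and the registry. Those clinics exist only in Cohorts 1 and 2, so 'only' may limit that one analysis and leave Cohort 3 to a fuller plan. Outcome 9.1 does not name Cohort 3, and referred Cohort 1 and 2 participants also attend a 2ww appointment. PPV and NPV depend on prevalence, which is a real reason to estimate them in a screening population. These points stand as far as they go: registry-based figures in Cohorts 1 and 2 are worth having. They do not remove the conflict, because the sentence as worded denies Cohort 3 the measure that Aim 3 assigns to it.

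Stronger readings are tempting, but the document does not support them:

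- That strip-negatives in Cohorts 1 and 2 are never verified. All self-testers except withdrawals are followed in the registry, and the sentence itself names it.
- That NPV and sensitivity there are 100% by construction. This would hold only for an analysis of clinic findings alone, and the plan includes registry data.
- That outcome 9 would go wholly unanalysed. Primary outcomes lists the measures, and Data collection covers Cohort 3 cystoscopy, imaging, cytology and staging. An article may leave further detail to the full documents.
- That PPV and NPV are known inputs to the economic model. Economic evaluation refers to feasibility outcome data in general and does not name them.

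**Conclusion.** The point holds as a contradiction between the analysis section and Aim 3, and as a poor fit with outcome 9.1. It rests on the text and needs no assumption. It is an error in what is stated, so it cannot be put down to condensation.

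Verification in Cohorts 1 and 2 is partial and differential. On the plan's own figure about 80% of strip-positives have no cystoscopy in the trial pathway, and neither do strip-negatives. Concealed positives in the glycosuria arm have no haematuria work-up. Their cancer status comes from passive registry follow-up only.

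The 1–6% verified depends on the assumed strip positivity. The cancer counts are illustrations under assumed prevalence and incidence. The cited yield came from men only, whereas Cohort 1 includes women and people from age 55. The Cohort 3 intervals assume 500 enrolled, as in Sample size(s); the Abstract has 500 kits posted, which at the implied 50% uptake would give 250.

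A reader might infer that Cohort 3 sensitivity and specificity can simply be combined with Cohort 1 and 2 prevalence to obtain screening PPV and NPV. They cannot be relied on for that: Cohort 3 is selected on haematuria, the sign the strip detects, so its accuracy need not carry over to asymptomatic people.

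**What to change.** - Delete the 'only' restriction. State that outcome 9.1 (sensitivity, specificity, PPV and NPV of self-testing, cytology and ultrasound) is estimated in Cohort 3 against the 2ww work-up.
- Report PPV and NPV for Cohorts 1 and 2 separately, labelled as registry-based screening-population estimates. Count cancers within a fixed time window from each participant's self-test date, stated in advance.
- Show the two Cohort 2 arms separately, since haematuria is acted on in one and concealed in the other.
- If Cohort 3 sensitivity and specificity are applied to Cohorts 1 and 2 at all, label this a sensitivity analysis and state the selection on haematuria.

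The cost is wording in the analysis section and the SAP. Data collection already covers Cohort 3 cystoscopy, imaging and cytology, and registry follow-up of self-testers. The downside is that the Cohort 1 and 2 NPV is presented as weaker evidence.

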### Economic evaluation

An early health economic model of haematuria screening for BCa in high-risk areas will be developed, including epidemiology, natural history and how this is affected by screening.^23^ The model design will be informed through analysis of other screening and diagnostic models in BCa. The model will be parameterised with the generated feasibility outcome data, supplemented by evidence from published literature. Bayesian calibration methods will be used for parameterisation of the disease natural history and screening model. The model will input to the design of and be refined using the subsequent trial outcomes.

### Patient and public involvement (PPI)

A group of nine PPI representatives were approached for initial review of the trial design, objectives, lay summary and survey questions, and their responses have been incorporated in the trial design. PPI members have also reviewed the participant facing documentation and provided feedback. One-to-one interviews and discussions with PPI members were held to obtain specific feedback on aspects of how the study is presented to potential participants. A PPI lead is included in the Trial Steering Committee (TSC).

### Trial organisation and administration

The trial is sponsored by the University of Sheffield and coordinated by the Cancer Research UK & King’s College London Cancer Prevention Trials Unit (CPTU). The central research nursing team and central cytology laboratory is based at Sheffield Teaching Hospital NHS Foundation Trust.

Two trial oversight groups provide guidance and management for the three cohorts. The Trial Management Group meet at least monthly and will comprise the CI, representatives from University of Sheffield and CPTU who are responsible for day-to-day management of the trial and carrying out the work detailed in the trial protocol. The purpose of the group is to ensure the trial is on track to its project plan and budget, manage trial risks, issues and mitigations and to escalate and report any major risks and issues to the TSC as necessary.

The TSC will concentrate on progress of the trial, adherence to the protocol, participant welfare and to assess the impact and relevance of any new information of relevance to the research question. The TSC will make recommendations, through its Chair, to the TMG, CI, trial sponsor, trial funders, CPTU and any other relevant party on all appropriate aspects of the trial. Most members of the TSC, including the Chair, will be independent of the trial, and will include lay/patient representation. Non-independent members will also be part of the TSC as observers. The final decision regarding whether the trial may continue is the responsibility of the TSC.

